### Variables

Detailed technical specifications, including the specific instruments for measuring each variable, as well as the level and type of measurement, can be found in the variable table of this document (Table 1).

**Table 1 pone.0290683.t001:** Variable table with detailed technical specification.

VARIABLE	CONCEPT DEFINITION	OPERATIONA L DEFINITION	VARIABLE TYPE	MEASUR EMENT SCALE	VARIABLE VALUE
**Eye Tracking** **(ET)**	Eye tracking involves a series of cameras and infrared or near-infrared light sources that track the gaze behavior of one eye (monocular) or both eyes (binoculars) [18].	Values obtained from Tobii Prolab software after registration Equipment: Tobii Pro Glasses 3.0	Quantitative	Interval	Numerical
**Neural Activity** **(NA)**	The pattern of neural activity involves a network of millions of neurons spread over a wide area. Activity patterns for different types of brain function overlap, based on the characteristics they share [19].	Voltage at locations F3, Fz, F4, C3, Cz, C4, P3, POz and P4. The electrode positions were organized in the following areas: frontal (F) left (F3) right (F4) center (Fz), centrotemporal (CT) left (C3) right (C4) center (Cz), parietotemporal (PT) left (P3) right (P4), parietooccipital center (PO) (POz). The EEG signal represents a wide range of frequencies that are commonly divided into different frequency bands, such as alpha band: 8–13 Hz, beta band: 13–30 Hz. Equipment: EEG Flexiful MCA Brainquick Micromed, nine electrodes will be placed according to the 10–20 system	Quantitative	Interval	Numerical
**Psychophysiological measures (PM)**	Psychophysiological measures provide a discrete and implicit way to determine the affective or cognitive state of the user on the basis of mind-body relationships. In reality, they are physical signals from the human body that are generated in response to psychological changes and are measured by special equipment in real time [20].	BVP, RR and SC levels obtained through the experimental conditions. Equipment. Decoder: PROCOMP THOUGHT TECHNOLOG Y Sensors: THOUGHT TECHNOLOGY Skin conductance sensor THOUGHT TECHNOLOGY respiratory sensor: TTH-SA931 THOUGHT TECHNOLOGY HR/BVP Sensor: THOUGHT TECHNOLOGY	Quantitative	Interval	Numerical
**Cognitive flexibility (CF)**	Cognitive flexibility is a critical executive function that can be broadly defined as the ability to adapt behaviors in response to changes in the environment[21].	Terman-Merrill Intelligence Scale. Equipment: Terman-Merrill test	Quantitative	Interval	Numerical
**Fluid intelligence (FI)**	Fluid intelligence (Gf) is defined as the ability to reason and the ability to generate, transform and manipulate different types of novel information in real time [22].	General score on the BETA 4 intelligence scale. Equipment: BETA 4 Test	Quantitative	Interval	Numerical
**Integrative Complexity (IC)**	Integrative complexity is a measure of the intellectual style used by individuals or groups in information processing, problem solving, and decision making[23].	CI scoring via AUTOIC software and manual coding of respondents. Equipment: Standard Dell Laptop	Quantitative	Interval	Numerical
**Decision** **Outcomes (DO)**	Fundamental properties of decisions that predict the performance and outcome of decisions in the real world [24].	We will compare the decisions of the GRs in the stimulus by comparing how their decisions behave against the set of robust options that we identified a priori, during the development of the stimulus. This difference in performance will be recorded across a wide range of outcome attributes, e.g. cost, positive impact, negative impact, damage avoided, and others. Equipment: Standard Dell Laptop	Quantitative	Interval	Numerical
**CIT Capacities (CCIT)**	Practical adaptation and self-organizing concepts, paradigms, algorithms, and implementations that enable or facilitate appropriate actions (intelligent behavior) in complex and changing environments [25].	CIT automation degrees; specifically: non automation, static scanning of system properties, unique "what if" simulation capabilities, scenario analysis, optimization, exploratory modeling, vulnerability scanning, and automatic identification of strong alternatives. Equipment: Standard Dell Laptop	Discreet	Interval	Alphanumeric

Eye Tracking (ET)

Eye tracking involves a series of cameras and infrared light sources that track the gaze behavior of one (monoc

ular) or both eyes (binocular) [18]. Using the CIT during a decision-making simulation introduces perceptual and cognitive demands on the participants, asked with making intervention decisions. Using a CIT to support decision-making involves a heterogeneous interaction between visual perception and multiple cognitive processes, including memory retrieval, problem-solving, and decision-making.

During the experiments, the following eye-tracking parameters will be collected, as recommended by Duerrschmid & Danner et al. [26]:

Time to first fixation (TTFF): The time elapsed between the appearance of the CIT and the user fixating their gaze for the first time on an area of interest, measured in seconds.

First Fixation Duration (FFD): The duration a user fixates on their first fixation point.

Fixation Duration (FD): The duration of a fixation, measured in seconds.

Fixation Count (FC): The number of fixations on a product.

Dwell Duration (DD): The time elapsed between the user’s first fixation on a product and the next fixation off the product, measured in seconds.

Dwell Count (DC): The number of "visits" to an area of interest (AOI).

These measurements offer new opportunities to gain insights into the interpretive process of participants during the decision-making situation, including differences between the research groups (RGs), the heuristics and biases involved in visual perception and decision-making, and the underlying mechanisms, such as search and recognition errors [27].

All measurements will be conducted using Tobii Pro Glasses 3.0 equipment, and the research team will receive proper training from the product suppliers.

Neural Activity (NA)

Neural activity will be recorded from nine scalp locations: F3, Fz, F4, C3, Cz, C4, P3, POz, and P4 using the Flexiful MCA Brainquick Micromed EEG. The nine electrodes will be placed according to the 10–20 system. The electrode positions are organized as follows: frontal (F) left (F3), right (F4), center (Fz); centrotemporal (CT) left (C3), right (C4), center (Cz); parietotemporal (PT) left (P3), right (P4); and parietooccipital center (PO) (POz). The EEG signal represents a wide range of frequencies commonly divided into different frequency bands, such as the alpha band (8–13 Hz) and the beta band (13–30 Hz).

The electroencephalographic recording will be performed by team members with trained experience in retrieving electroencephalographic records as part of their curriculum.

The electroencephalographic recordings will be conducted simultaneously with the biofeedback devices and the eye-tracking glasses, ensuring no cable crossing. The recordings will take place in a spacious environment (approximately 50m2) to minimize interference from other electronic devices.

Psychophysiological measures (PM)

Psychophysiological measures offer a discrete and implicit means to determine the affective or cognitive state of the user based on mind-body relationships. Essentially, they are physical signals the human body generates in response to to psychological changes and are measured in real-time using specialized equipment [20]. In this specific study, we will focus on three types of psychophysiological measures: Blood Pressure Volume (BVP), Respiration Rate (RR), and Skin Conductance (SC).

Executive Control (EC)

The Terman-Merrill Intelligence Scale will be administered to assess the executive control and cognitive flexibility of the participants. This intelligence scale is derived from the Binet scale and has been adapted and standardized for the Mexican population. The scale provides two overall scores: a) general cognitive intelligence (CI), and b) learning capacity. Additionally, it provides individual scores for ten cognitive characteristics of the respondent:

InformationComprehensionVerbal meaningsLogical selectionArithmeticPractical judgmentAnalogiesSentence orderingClassificationSeriation

These scores will help to assess the participants’ cognitive abilities related to executive control and cognitive flexibility.

Fluid intelligence (FI)

The fluid intelligence of participants, which refers to their ability to think logically, analyze, and solve novel problems independently of prior knowledge, will be measured using the Beta 4 Intelligence scale.

This is a non-verbal intelligence scale that consists of five subscales designed to assess the respondent’s ability to perform various tasks:

Decryption keysNon-logical imagesSimilaritiesCompletionProgression

These subscales provide valuable insights into the participant’s cognitive abilities and capacity to respond to different types of tasks, thereby assessing their fluid intelligence.

Integrative Complexity (IC)

The research team will evaluate existing frameworks for measuring integrative complexity, such as Conway et al.’s [28] automated framework and develop a procedure to measure the level of integrative complexity exhibited by participants when they engage in problem-solving tasks using laboratory-tested decision-making tools. To achieve this, we will record the experimental sessions and the participants’ response and utilize this data to automatically generate written transcripts of the sessions (our laboratory already possesses this capability). These transcripts will then be processed using word and phrase searches to enable the assessment of integrative complexity in individuals based on Conway’s AUTOIC tool.

Decision Outcomes (DO)

We will compare the decisions made by the research groups (RGs) in response to the stimulus by evaluating how their decisions align with the set of robust options identified a priori during the development of the stimulus. This comparison will involve assessing differences in performance across a wide range of outcome attributes, including but not limited to cost, positive impact, negative impact, damage avoided, and others.

The data relevant to the decisions will be analyzed by the research team as well as an external expert whose work focuses on the development of computational methods for studying social-ecological resilience under uncertainty and complexity, particularly in the context of developing simulation models for analyzing policy decisions.

CIT Capacities (CCIT)

The CIT supporting the stimulus situation will exhibit varying degrees of automation. The degrees of automation will be categorized as follows: no automation, static scanning of system properties, unique what-if simulation capabilities, scenario analysis, optimization, exploratory modeling, vulnerability analysis, and automatic identification of strong alternatives.

The research team will specifically design the tool for the decision-making task using an expert system based on artificial intelligence (SSEE) framework. These types of systems utilize programming to simulate the knowledge of an expert through artificial intelligence, enabling users to solve specific problems effectively.

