### Hypothesis

#### Null hypothesis

There is no effect of the CITs on the decisions that are made in complex and uncertain scenarios.

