## Study design

### Study description

This phase 0 randomized controlled study that utilizes the Solomon cluster experimental design to assess the relationship between using CITs and decisions made during complex and uncertain situations. Potential populations for this study include undergraduate and graduate students, and decision-makers, given their close involvement in day-to-day decision-making processes. Participants will engage in decision-making strategies using a standardized interface, focusing on a classic decision-making problem known as Ellsberg’s paradox. No incentives or monetary resources will be at stake during the study. The participants’ psychophysiological responses will be recorded: blood pressure volume, respiration rate, skin conductance level, and EEG activity. Additionally, participants will complete standardized pencil-and-paper intelligence tests.

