### Research methodology

The research team will design a decision-making stimulus situation based on standardized decision-making paradigms validated in the existing literature, such as Ellsberg’s paradox. The characteristics of this decision-making situation will include non-linear behavior, multi-criteria results, ambiguity, and uncertainty. The stimulus parameters and narrative will be designed through computational experimentation to identify viable and robust interventions to serve as a baseline for analysis.

The stimulus situation will always be defined by choice interfaces that do not threaten the participants and will not involve monetary resources or real economic gains. These interfaces will be developed based on previously standardized situations described in the available literature, with defined parameters of ambiguity and validated performance in computational interfaces, such as Ellsberg’s paradox.

The Ellsberg paradox is an experimental challenge where participants make decisions about a possible outcome based on the probability of an event occurring [14]. This paradox is frequently used in decision-making theory [15,16]and has modulations in terms of ambiguity (amount of information offered to the decision-maker) and uncertainty (random result).

The experimental task of the Ellsberg paradox involves making a series of bets (without involving economic resources, only predictions) on the random selection of a colored ball in a lottery. The balls are red, green, or blue, and participants receive information about the total number of balls in a container, which varies in each round. Three decision conditions are presented to the participants. In the first condition, complete information is provided for each betting option, allowing participants to estimate which ball is most likely to be chosen. In the second condition, ambiguity is introduced by combining the frequency information of two balls into a single category, making it impossible for participants to determine which ball is more frequent and thus has a higher probability of being chosen in the lottery. In the third condition, participants are provided with a decision support tool that presents information about the probability of selecting each ball, considering all possible container frequency combinations (see Appendix 1 for images of the interface).

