### Statistical analysis techniques

#### Methods and models of data analysis according to the type of variables

We will utilize a cognitive model to integrate various data obtained from the study. Cognitive models describe how different aspects or variables interact and contribute to the observed behavior in empirical studies. Various influences come into play during the decision-making process, resulting in specific behaviors. Cognitive models provide valuable insights into the interconnected cognitive processes that contribute to the observed behavioral outcomes [5]. In this study, we propose to develop the following model:

$$DO_{i}=\overset{N}{\underset{j=1}{\sum }}\overset{P}{\underset{i=1}{\sum }}\overset{T}{\underset{k}{\sum }}f_{i}(f_{j}(ET),f_{j}(NA),f_{j}(EC),f_{j}(FI),CIT_{k})+\varepsilon$$

Therefore, a set of models will be trained using experimental data to describe the outcomes of individual decisions (i.e. *DO_i_*). Each outcome will be modeled as a combination of the aggregate characteristics of the research groups participating in the study (i.e., N) and their interactions with different versions of CIT supporting the war game (i.e., T), using a set of math functions. i.e., P) to describe these interactions (i.e., P).

Fig 1 presents a schematic example illustrating the expected outcomes of this research agenda. The scenario depicted in this figure suggests that the advantages of CITs peak at different levels of automation, depending on the specific planning team contexts. For instance, a group that with a substantial amount of pre-existing information may derive maximum benefits from CITs with moderate automation, as the abundance of available data may be associated with higher cognitive abilities. Conversely, a group with limited access to data may benefit from higher levels of automation to compensate for the lack of existing information. However, if the tools become overly complex for this group, the advantages of automation may diminish.

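### Decision Outcomes is to be recorded on an open list of attributes that the no-stakes ball-colour task does not yield, and no score is fixed for the one part that it can yield

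*Protocol article*

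**What the plan says.** The null hypothesis reads "There is no effect of the CITs on the decisions that are made in complex and uncertain scenarios". It names no measure.

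The measure comes from the Variables section. The Decision Outcomes (DO) text describes "evaluating how their decisions align with the set of robust options identified a priori during the development of the stimulus". It then says that performance will be assessed on attributes "including but not limited to cost, positive impact, negative impact, damage avoided, and others". Table 1 gives the same list as examples and states: "This difference in performance will be recorded across a wide range of outcome attributes".

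The section on methods and models of data analysis puts DO on the left-hand side of its only equation: "a set of models will be trained using experimental data to describe the outcomes of individual decisions".

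The Research methodology section describes the Ellsberg task as "making a series of bets (without involving economic resources, only predictions) on the random selection of a colored ball in a lottery". The Study description adds: "No incentives or monetary resources will be at stake during the study". In the ambiguous condition two colours are merged into one category, "making it impossible for participants to determine which ball is more frequent".

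**The concern.** The scoring text and the task text do not describe the same experiment. A colour prediction produces a choice, followed by a random draw. Cost, impact of either sign and averted damage belong to a simulation in which a decision-maker intervenes in some system. Two other places point the same way. The analysis section refers to versions of the CIT that support a war game, and the eye-tracking text refers to intervention decisions.

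At stake is the variable that carries the main hypothesis. Someone following Table 1 with this task could not fill in the named attributes. They would have to choose for themselves what stands in for them. The list has no end, so a single null hypothesis faces an unspecified number of outcomes.

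**Working it through.** **The plan's own figure.** The only figure is the head count: 4 groups × 30 = 120, which checks. No significance level, power, effect size or standard deviation is given, so there is no power statement to reproduce. The check is mainly a comparison of texts.

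**Step 1: does DO carry the hypothesis?** The objective and both hypotheses concern decisions. Table 1 also lists eye tracking, neural activity, psychophysiological measures, cognitive flexibility, fluid intelligence, integrative complexity and CIT capacities. None of these measures the decision itself. DO does, and it is the modelled outcome. The article never calls it primary; that role is inferred.

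**Step 2: what each element needs and what the task supplies.**

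| Element of DO | Needs | Supplied by the described task |
|---|---|---|
| Cost | A resource spent or a price attached to an option | No money or incentive; bets are predictions only |
| Positive or negative impact | A consequence of the choice for some system or party | None described; the choice does not alter the draw |
| Damage avoided | A hazard that the choice can reduce | None described |
| Agreement with robust options set in advance | A recorded choice, a defined option for each round, a scoring rule | The choice exists; the options and the rule are not stated |

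Only the last row can be scored, and it is incomplete.

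**Step 3: can the last row be completed for ambiguous rounds?** Suppose a container holds N balls, r of a known colour and m of two merged colours, with N = r + m. The third task condition already shows probabilities over all possible combinations. Giving each combination equal weight (an assumption), each merged colour has expected count m/2:

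- known colour: r/N
- each merged colour: m/(2N)

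The known colour is the best bet if r > m/2. If r < m/2, the two merged colours tie. So a robust option can be defined, but ties are built in. A participant guessing evenly among three colours matches a single best option with probability 1/3 and a two-way tie with probability 2/3. The baseline score therefore depends on ambiguity, which the group comparison must take into account.

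**Step 4: illustration of an open list.** Assume independent attributes, each tested at 5%. The chance of at least one false rejection is 1 − 0.95^k:

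- k = 4 (those named): 1 − 0.95^4 = 0.185
- k = 10 (arbitrary): 1 − 0.95^10 = 0.401

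Positive correlation lowers both.

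**Step 5: illustration of one score.** Comparing RG2 and RG3 with RG1 and RG4 gives 60 against 60. At an assumed two-sided 5% and 80% power, the detectable standardised difference is (1.960 + 0.842) × √(2/60) = 0.51. Splitting 5% over four attributes gives (2.498 + 0.842) × √(2/60) = 0.61.

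**The case against.** The strongest reply is that DO already has an anchor. Decisions are compared with robust options identified in advance, and the attributes appear in Table 1 only as examples. The stimulus is still to be designed, the Research methodology section says that it will have multi-criteria results, and the appendix with the interface is not shown. The study is exploratory and its main objective is to describe. Detailed scoring rules are often left to a fuller document.

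Much of this stands, and it rules out three stronger readings that a reader might infer.

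- **That the hypothesis has no usable endpoint or that DO cannot be computed at all.** The anchor is a usable starting point, and the fix builds on it.
- **That the plan carries a 19% to 40% false-positive risk.** The article states no significance level and no attribute-by-attribute test of the null. Those figures show what an open list could do under assumptions, not what is planned.
- **That DO would measure luck.** The article says that the CIT returns feedback on results to participants. Nothing says that the random draw enters DO.

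The mismatch itself does not fall away. A bare reference to multi-criteria results gives the ball task no cost, impact or damage component. Both definitions of DO route the performance difference through the attributes. This is stated text that does not fit the stated task, rather than detail left for later.

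**Conclusion.** The point holds as an inconsistency between the scoring of DO and the task, with no score fixed for the part of DO that the task can produce. It should be corrected before enrolment. It rests on two inferences: that DO is the main outcome, from the hypothesis and the model; and that the task is as described, with no undisclosed cost or damage component.

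Its size cannot be reduced to a number. All four named attributes are unsupported by the described task, and the total number of attributes is undetermined. The error rates and detectable differences above are illustrations under assumed inputs. The exploratory label softens the multiplicity argument but does not make the attributes measurable.

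**What to change.** In Table 1 and the DO text:

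1. Define the main DO as the proportion of rounds in which a participant's bet matches the robust option for that round. Set the options before enrolment and score from the information displayed, not from the draw.
2. In ambiguous rounds, derive the robust option from the probabilities over all possible container combinations, and count any tied best option as a match.
3. Record choices in the same way in all four groups. The article describes entry of decisions into the CIT, which only two groups use, so recording in RG1 and RG4 needs to be stated.
4. Make the main contrast the CIT groups (RG2, RG3) against the groups without it (RG1, RG4), accounting for ambiguity.
5. Label any other attribute exploratory and delete those that the task cannot produce.
6. Reconcile the war-game and intervention-decision wording with the Ellsberg task.

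The cost is mostly wording, plus a recording arrangement for the two groups without the CIT. Other attributes become exploratory, which loses little because none was given confirmatory status. The score may show a ceiling effect in the full-information groups, where the likeliest ball can be worked out. In ambiguous rounds the robust option follows the same calculation that the tool displays, so RG3's score will partly reflect uptake of the tool's output and should be read that way.

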#### Secondary objectives

Determine the relationship of the experimental parameters of the TICs with a positive impact of decision-makers’ ability to deal with a complex and uncertain environment.

Determine the combination of experimental parameters of the TICs that positively impact the level of integrative complexity of individuals when faced with an ambiguous, or deeply uncertain problem.

Determine the combination of experimental parameters of CITs that lead to mistrust, excessive technological dependence, model rejection or stagnation in complex and uncertain environments.

Evaluate the marginal impact of CIT components on people’s cognitive bandwidth in complex and uncertain decision-making environments.

Evaluate the CIT components’ marginal impact on the integrative complexity of people in complex and uncertain decision-making environments.

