### Rationale for stratification factors

The participants in this study will consist of undergraduate or graduate students, and professionals from Tecnológico de Monterrey. All participants will be recruited through their teachers using a script and subsequently contacted via email to schedule an appointment in the study environment. The study topics will not be disclosed in class, and there will be no rewards or penalties for participation. All participants must volunteer and provide informed consent approved by the ethics committee of Tecnológico de Monterrey in Mexico.

One hundred and twenty (undergraduate and graduate students) will be divided into four research groups (RG). Each RG will comprise 30 individuals, with equal representation of 15 men and 15 women from various disciplinary backgrounds. The assignment of participants to each research group will adhere to the following experimental criteria:

RG 1: No computational system or ambiguity

RG 2: Unambiguous computer system

RG 3: Computational system with ambiguity

RG 4: Ambiguity without a computer system

Participants in the research groups will be carried out randomly while considering factors such as age, educational level, and sex to reduce intergroup variability. Each subject will belong to only one group and will participate in a single experimental session to avoid maturation and memory effects.

Regarding cognitive abilities, these factors will be analyzed post hoc to identify cognitive patterns associated with using CITs within the studied sample. Stratification based on cognitive conditions will not be conducted a priori, as the literature reports contradictory results between these conditions and the use of CITs and integrative complexity [8,9].

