The CIT will be an expert system based on artificial intelligence (SSEE), utilizing previous knowledge from the literature and the response options of the stimulus situation. Artificial intelligence will simulate the knowledge of an expert to solve a specific problem effectively. The resulting CIT will be unanimously validated by three expert judges in the use of computational tools in decision-making.

Participants will be presented with the interface, and only two research groups (RGs) will be asked to use the CIT to study the situation. Participants will have time to explore the decision-making situation and be guided through various phases of the interface. The decisions made by the participants will be entered into the CIT, which will provide feedback on the results of their decisions.

The experimental procedures will be divided into three steps, following the Solomon group experimental design. According to McCambridge et al. [17], Solomon’s 4-group design involves randomly assigning participants to four possibilities: (a) an experimental group with evaluations, (b) an experimental group without evaluations, (c) a control group with no assessments, and (d) a control group with no assessments. This design enhances internal validity by controlling for the effects of the baseline estimate and the interactions between the intervention and the baseline assessments.

Given that the present study examines the use of CITs in situations of ambiguity, the Solomon group design is an appropriate measure to observe the interaction between these variables within a single experimental design. The following groups will be established for the sample:

RG 1: No computational system or ambiguity

RG 2: Unambiguous computer system

RG 3: Computer system with ambiguity

RG 4: Ambiguity without the computer system

The inclusion of participants in the research groups will be carried out randomly, considering stratification and pairing factors based on their age, educational level, and sex to reduce intergroup variability. Each participant will belong to only one group and will participate in a single experimental session to avoid maturation and memory effects.

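### The secondary objectives, the eight-degree CIT variable and the model need variation in automation, but the described design compares one tool with no tool

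*Protocol article*

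**What the plan says.** **What the objectives, variable and model call for.**

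- Secondary objectives: one aim is "Determine the combination of experimental parameters of CITs that lead to mistrust, excessive technological dependence, model rejection or stagnation". Another asks which parameter combination raises integrative complexity. Two more ask for the marginal impact of CIT components, on cognitive bandwidth and on integrative complexity.
- Variables, CIT Capacities (CCIT), and the matching row of Table 1: "The CIT supporting the stimulus situation will exhibit varying degrees of automation". Eight degrees follow, starting at no automation and ending with a tool that finds strong alternatives by itself.
- Statistical analysis techniques: decision outcomes are modelled through "interactions with different versions of CIT supporting the war game (i.e., T"), with a CIT term indexed by version. The text on Fig 1 describes benefits that peak at different automation levels.

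**What the design provides.**

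- Rationale for stratification factors: the 120 students are split four ways, and the size of each part is fixed: "Each RG will comprise 30 individuals, with equal representation of 15 men and 15 women".
- Research methodology: the groups are defined only by computer system (yes or no) and ambiguity (yes or no), for example "RG 2: Unambiguous computer system". Of the four, "only two research groups (RGs) will be asked to use the CIT to study the situation". The procedure steps add that the others have no access to it.
- Research methodology, on the Ellsberg task: "participants are provided with a decision support tool that presents information about the probability of selecting each ball". The tool is spoken of in the singular throughout, as one expert system validated by three judges.
- Each participant belongs to one group and attends one experimental session.

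**The concern.** A study can estimate the effect of a feature only if the feature differs between participants, or between occasions within a participant. Automation degree is defined as a study variable and indexed in the model, yet the described assignment varies only whether the tool is present. This is not a detail that an analysis plan could supply later: analysis cannot create variation that was not assigned.

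What is at stake is the reading of the results. If the secondary objectives are reported as worded, a contrast between one tool and no tool could be presented as evidence on which automation level or parameter combination helps, or which breeds mistrust or dependence. The Discussion expects designers of such tools to use the results, so the distinction matters to them.

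The model text also refers to a war game, while the task described is an Ellsberg ball lottery. The analysis section therefore appears to describe a different experiment from the one in the design section.

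**Working it through.** **1. Reproduce the sample size.** Four groups of 30 (Rationale for stratification factors): 4 × 30 = 120, which matches the stated total. This is only a count. The article gives no alpha, power or effect size, so there is no power calculation to reproduce.

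**2. Count exposure to the tool.** RG 2 and RG 3 use it: 2 × 30 = 60. RG 1 and RG 4 do not: 2 × 30 = 60.

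**3. Count the distinct conditions.** Tool (no, yes) × ambiguity (no, yes) = 4. However the model is written, these groups support at most four independent group-level parameters.

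**4. Write out the model that eight degrees would need.** Take no automation as the reference, which leaves 8 − 1 = 7 automated degrees.

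- Main effects: 1 intercept + 1 ambiguity term + 7 degree indicators = 9 columns.
- With degree-by-ambiguity interaction: 9 + 7 = 16 columns.

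**5. Fill in the design as described.** One tool at one degree means that six of the seven indicators are zero for all 120 participants, and so are their six interaction columns.

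- Main effects: rank 9 − 6 = 3 (intercept, ambiguity, tool versus none).
- With interaction: rank 16 − 6 − 6 = 4 (the same three plus tool by ambiguity).

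A numerical rank check of the two design matrices gave the same values, 3 and 4.

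**6. Translate rank into questions that can be answered.**

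- Automated degree versus none: 1 of 7 contrasts estimable, namely this tool versus none.
- Automated degree versus another automated degree: 7 × 6 / 2 = 21 contrasts, 0 estimable.
- Degree-by-ambiguity: 1 of 7 contrasts estimable.
- An automation optimum: not estimable, since it needs several degrees to be observed.
- A combination of CIT parameters: not estimable, since no parameter of the tool is varied.

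**7. Set this against the objectives.** The main objective and the hypotheses ask whether CITs affect decisions. The 60 versus 60 comparison addresses that, and the four groups also give the interaction with ambiguity. The objectives on parameter combinations ask for contrasts from the empty part of the list in step 6. The objectives on components can be met only for the tool as a whole, because no component is added or removed separately.

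**The case against.** **Automation could vary within a session.** The task runs over a series of bets, participants pass through phases of the interface, and the interface images sit in an appendix that is not shown. The statement about varying degrees could describe one tool that changes as the session proceeds. This stands in part: such variation is not excluded. But it is nowhere described. What is said to change from round to round is the number of balls, and the tool is given a single function. It would therefore be too strong to say that automation effects can never be estimated in this study; the supportable claim is that they cannot be estimated from the design as described.

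**The objectives speak of parameters and components, not automation degrees.** This is correct, and the Research question section defines marginal impact as a difference from control. On a lenient reading, a combination might mean tool by ambiguity, which is estimable. But the objectives refer to parameters of the tools, and the article names CITs and ambiguity as two separate controlled variables. The lenient reading becomes sound only once the objectives are reworded that way.

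**The study is exploratory.** That lowers the demand for power. It does not make a contrast estimable when nothing varies.

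**Fig 1 is only a schematic.** This stands. The text presents it as an illustration for a research agenda, so a peak in benefit is not a declared outcome or hypothesis. The conflict does not depend on it.

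**Two further inferences a reader might draw are not supported.** Table 1 labels the list of capabilities as interval-scaled, which might suggest equally spaced linear coding. No section specifies such coding, the model's functions are left open, and every row of the table carries the same label. One might also compute the power lost by spreading the 60 tool users over seven degrees. The protocol proposes no such split and states neither alpha nor power, so such a figure would not measure this defect.

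**Conclusion.** The contradiction is real, and the text is wrong as it stands. The objectives on CIT parameter combinations and components, the eight-degree CCIT variable and the model's sum over T need variation in automation that the described design does not contain.

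In size, the design supports one tool-versus-none contrast (60 versus 60) and one interaction with ambiguity. None of the 21 contrasts between automated degrees can be estimated. These counts use only group sizes and definitions in the article. They assume that the same tool, at one fixed degree, is used in RG 2 and RG 3 and throughout the session, as the text describes.

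A reader might infer that the trial as a whole cannot answer its question. The documents do not support that: the main objective, the hypotheses and the tool-by-ambiguity interaction remain estimable. The defect is confined to secondary objectives, one variable definition and the model.

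**What to change.** 1. Define CCIT in the Variables section and Table 1 as a binary factor: no tool, or this probability-display tool.
2. Restate the affected secondary objectives as the effect of this one tool, and its interaction with ambiguity, on integrative complexity, cognitive bandwidth, and mistrust or dependence.
3. Rewrite the model to match: remove the sum over T and the reference to a war game.
4. Mark Fig 1 as a direction for future research, not an expected outcome of this study.

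The cost is wording in the objectives, Table 1, the model and the Fig 1 text, and narrower claims about automation. Sample size and procedures do not change.

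If automation is in fact varied within sessions, state which degrees are used and how they are assigned to rounds, then analyse degree as a categorical factor labelled exploratory. Adding tool versions that do not yet exist would cost more than wording, because each would have to be built and put through the validation by expert judges that the article requires.
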